### Recruitment

Awareness sessions and one-on-one interactions will be held for outpatients to facilitate recruitment. Screening camps will also be conducted in local panchayats to boost enrollment and support the timely completion of recruitment.

### Randomization and Allocation

After getting consent from parents or guardians, participants will be randomized and allocated to the study group or control group in a ratio of 1:1 with the help of serially numbered opaque sealed envelopes. Due to the nature of the trial, participant and investigator blinding is not feasible.

### Concomitant Medication

Parents will be advised against self-medicating their children and will instead be encouraged to consult the investigator for any symptoms. The investigating physician will document any prescribed medications.

### Ancillary and Posttrial Care

All clinical trial participants will receive appropriate ancillary care, including management of any adverse events or unrelated health issues that arise during the study. Posttrial participants will be given appropriate treatment for management of their condition, if required, or will be referred to appropriate health care services, in accordance with ethical standards.

### Data Collection

#### Baseline Assessments

At baseline, after recording the medical history, other details, such as demographic characteristics, Ayurveda parameters, anthropometric measurements, the WAZs, and illnesses during the past 3 months, will be collected. Laboratory investigations will be performed for participants whose parents provide consent.

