### Outcome Measures

The primary outcome measure is the proportion of participants attaining a change in the weight-for-age *Z* score (WAZ) by ≥0.5, as per WHO reference standards, from baseline to weeks 12 and 16. The secondary outcome measures include changes in anthropometric measurements (weight in kg, height in cm, and midupper arm circumference in cm), which will be assessed every 2 weeks for 12 weeks, followed by assessment at week 16. Change in the frequency of illnesses will be assessed at baseline, week 12, and week 16 using a predesigned table that records the frequency and duration of illnesses. Assessment of safety (complete blood count [CBC], liver function test [LFT], renal function test [RFT], and serum electrolytes) will also be performed at baseline and week 12 in a small proportion of participants whose parents provide consent.

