#### Follow-Up Assessments

All participants will undergo follow-up assessments on days 14, 28, 42, 56, 70, 84, and 112. Concomitant medication, rescue medication, drug compliance, and adverse drug reactions or adverse drug events will be assessed during the follow-up visits. Laboratory investigations will be performed at the day 84 visit for those who underwent baseline laboratory assessments (Table 1).

**Table 1 table1:** Study schedule.

Assessments	Screening or baseline	Follow-up		
		Weeks 2-10 (days 14, 28, 42, 56, and 70)	Week 12 (day 84)	Week 16 (day 112)
Informed consent from parent	✓			
Laboratory investigations (for those who are willing)	✓		✓	
Demographic characteristics and medical history	✓			
Weight-for-age *Z* score	✓		✓	✓
Anthropometric measurements (weight, height, midupper arm circumference, and BMI)	✓	✓	✓	✓
Assessment of illness frequency	✓		✓	✓
*Dosha*, *dhatu*, and *srotopareeksha* assessment	✓			
Assessment of concomitant medications		✓	✓	✓
Assessment of rescue medications		✓	✓	✓
Assessment of adverse drug reactions and adverse events		✓	✓	✓
Drug compliance assessment		✓	✓	
Dispensing of trial drug and compliance reporting form	✓	✓		

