### Statistical Methods

The primary outcome of the study, namely, the proportion of participants achieving an improvement in the WAZ of ≥0.5, will be analyzed using an intention-to-treat approach. Between-group comparisons for the primary binary outcome will be performed initially using the chi-square test, followed by multivariate logistic regression to estimate adjusted effect sizes after controlling for important covariates, including study center, baseline, WAZ, age, sex, and other clinically relevant variables. This will be done in the following steps:

Step 1: an unadjusted between-group comparison will be performed using the chi-square test to examine the crude difference in the proportion of participants achieving the primary outcome between the intervention and control groups. This provides transparency and allows readers to evaluate the raw effect.Step 2: multivariate logistic regression will be used to estimate the adjusted odds ratio and 95% CI, while controlling for the following prespecified covariates: study center, baseline WAZ (continuous), age (months), sex, baseline nutritional status category, socioeconomic status, and educational status of parents. The adjusted analysis represents the primary analytic result and will be emphasized in reporting and interpretation.

For the secondary outcomes, within-group pre-post changes will be examined using a paired *t* test or Wilcoxon signed-rank test, as appropriate, and will be reported for descriptive purposes. For parameters assessed at multiple follow-up time points, repeated-measures ANOVA or the Friedman test will be applied to assess temporal trends. All analyses will be performed using SPSS (version 29.0; IBM Corp), and statistical significance will be assessed at α=.05 (2-tailed).

Participants who withdraw, are lost to follow-up, or do not complete the week 12 assessment will be documented, and reasons for dropout will be recorded. Dropout rates and reasons will be presented by study group in the CONSORT (Consolidated Standards of Reporting Trials) flowchart.

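### Illness frequency is compared across assessments with no common look-back window or rate scale, and only within-group and trend tests are named for it

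*Protocol article*

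**What the plan says.** Three parts of the protocol article bear on this outcome.

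- **Baseline window.** Baseline Assessments collects "illnesses during the past 3 months".
- **Later assessments.** Under Outcome Measures, "Change in the frequency of illnesses will be assessed at baseline, week 12, and week 16 using a predesigned table". The instrument is described only by its content: "using a predesigned table that records the frequency and duration of illnesses". Follow-Up Assessments sets the visit days: "All participants will undergo follow-up assessments on days 14, 28, 42, 56, 70, 84, and 112". In Table 1 the row "Assessment of illness frequency" is ticked at baseline, week 12 (day 84) and week 16 (day 112), and not in the weeks 2-10 column. No look-back period is given for week 12 or week 16.
- **Analysis.** For secondary outcomes, Statistical Methods says "within-group pre-post changes will be examined" by paired t or Wilcoxon signed-rank test, and that these "will be reported for descriptive purposes". For parameters with several follow-up points, "repeated-measures ANOVA or the Friedman test will be applied to assess temporal trends". Significance for all analyses is judged at two-sided 0.05. No between-arm test is named for illness and no rate per unit of time is mentioned. The Discussion (Anticipated Findings) nevertheless expects the intervention to lower illness frequency relative to control.

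**The concern.** A count of illnesses depends on how long one looks. The baseline count has a fixed 3-month window, and the last two assessments are 28 days apart. Pre-post and trend tests on counts are interpretable only if each count covers the same length of time or is turned into a rate. The article states neither.

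At stake is a named secondary efficacy outcome. If the windows differ, the tests that are specified respond to window length as well as to illness. The comparison that randomization protects, and that the stated hypothesis needs, is the one with no named test.

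**Working it through.** The plan gives no figure for illness frequency, so there is nothing of its own to reproduce. The check is the ratio of observation windows at a constant illness rate, followed by a simulation of the named tests.

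**Inputs from the article**
- Baseline window: 3 months, taken as 91 days (Baseline Assessments).
- Illness assessments at day 84 and day 112 (Outcome Measures; Table 1). Interval: 112 - 84 = 28 days.
- 200 children randomized 1:1, so about 100 per arm (Abstract; Trial Design).
- Two-sided alpha 0.05 (Statistical Methods).

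**Assumptions, because the article is silent**
- Week 12 counts illnesses since baseline (84 days).
- Week 16 follows one of three readings: (A) since week 12, (B) past 3 months, (C) since baseline.
- Illness rate between 0.5 and 3 episodes per 3 months, unchanged over time and equal in both arms.

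**Expected count relative to baseline = window / 91**

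| Assessment | Window (days) | Ratio | Apparent change at a constant rate |
|---|---|---|---|
| Week 12, since baseline | 84 | 84/91 = 0.92 | -8% |
| Week 16, reading A | 28 | 28/91 = 0.31 | -69% |
| Week 16, reading B | 91 | 91/91 = 1.00 | none |
| Week 16, reading C | 112 | 112/91 = 1.23 | +23% |

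Under A, a child averaging 1.0 episode at baseline averages 0.31 at week 16 with no change in illness rate.

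Under B, the recall reaches back to day 112 - 91 = 21. Days 21 to 84 were already covered at week 12: 84 - 21 = 63 days, or 9 weeks. So 63 of the 91 days counted at week 16 lie before the follow-up period begins.

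**Simulation with no true change** (1,000 runs per setting, 100 children per arm, rates of 0.5, 1, 2 and 3 episodes per 3 months, Poisson and gamma-Poisson counts)

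| Test | Rejection at 0.05 |
|---|---|
| Baseline vs week 16, reading A, paired t or Wilcoxon | 98.8% to 100% |
| Baseline, week 12, week 16 (reading A), Friedman | 98.5% to 100% |
| Baseline vs week 12, paired t | 7% to 17% |
| Baseline vs an equal 91-day window, paired t | 4.5% to 6.1% |
| Between-arm comparison of change to week 16, reading A | 4.6% to 6.6% |

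Rejection returns to about 5% once the windows are equal, so window length alone causes the excess. Repeated-measures ANOVA was not simulated. It tests the same three means, which under A stand at 1, 0.92 and 0.31 of baseline.

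**The case against.** The strongest reply is that the recall period belongs to the predesigned table. That table is not shown, and a journal article may properly leave such a detail to the full protocol or the analysis plan. This stands as far as it goes: an unstated window alone would not be a finding, and the word frequency could mean a rate. But the article itself fixes a 3-month baseline, a 28-day final interval and a set of tests across the three assessments. Readings A and C distort those tests. Reading B leaves the mean alone but makes week 16 largely a second count of week 12.

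Three stronger conclusions are tempting, and the documents do not support them.

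- **That a fall in illness will appear in both arms.** This follows only under reading A. Reading B gives no artefact in the mean, and reading C gives a rise.
- **That such a fall would be taken as a treatment effect.** The paired tests are labelled descriptive, the hypothesis is framed against control, and the artefact would appear equally in the control arm. A between-arm comparison stays near nominal. The label is only a partial defence, however: it is attached to the paired tests and not to the trend tests, and no between-arm illness test is named.
- **That on-study illness is captured more fully through the 2-weekly visits than by baseline recall.** Table 1 schedules no illness-frequency assessment at those visits. Adverse events are checked there, but nothing says they feed the illness table.

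It is also fair to say that the end-of-treatment contrast, baseline against week 12, is nearly matched. The large figure concerns only week 16.

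**Conclusion.** The point holds in conditional form. The article does not put illness frequency on a common window or rate scale, and the within-group and trend tests it names are sensitive to that.

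The size depends on the unstated week-16 look-back: an apparent 69% fall in both arms if it starts at week 12, an apparent 23% rise if it starts at baseline, and no mean artefact but 9 weeks of double counting if it is a 3-month recall. The near-certain false rejection belongs to the first reading only. It does not depend on the exact illness rate within 0.5 to 3 episodes per 3 months. For week 12 the mismatch is small (ratio 0.92, assuming a count since baseline).

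This affects one secondary outcome. It should be corrected before analysis.

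**What to change.** 1. State the look-back period that the illness table uses at week 12 and at week 16.
2. Make the illness analysis a between-arm comparison of episodes per child-time over two non-overlapping periods, day 0-84 and day 84-112. A suitable model is negative binomial regression with arm, centre and the 3-month baseline count as covariates and log days observed as offset. Report rate ratios with 95% CI, and treat days of illness in the same way. Other rate-based methods would also serve; the essentials are the time scale and the comparison between arms.
3. Do not test raw change from baseline across unequal windows. Within-group figures may still be shown descriptively as episodes per child-month.

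The cost is mainly analysis wording. The table already records frequency and duration, and the article expects to submit findings only in December 2026. The one practical limit is that, if week 16 used a 3-month recall, episode dates are needed to separate the two periods. Without them, analyse day 0-84 only.

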#### Follow-Up Assessments

All participants will undergo follow-up assessments on days 14, 28, 42, 56, 70, 84, and 112. Concomitant medication, rescue medication, drug compliance, and adverse drug reactions or adverse drug events will be assessed during the follow-up visits. Laboratory investigations will be performed at the day 84 visit for those who underwent baseline laboratory assessments (Table 1).

**Table 1 table1:** Study schedule.

Assessments	Screening or baseline	Follow-up		
		Weeks 2-10 (days 14, 28, 42, 56, and 70)	Week 12 (day 84)	Week 16 (day 112)
Informed consent from parent	✓			
Laboratory investigations (for those who are willing)	✓		✓	
Demographic characteristics and medical history	✓			
Weight-for-age *Z* score	✓		✓	✓
Anthropometric measurements (weight, height, midupper arm circumference, and BMI)	✓	✓	✓	✓
Assessment of illness frequency	✓		✓	✓
*Dosha*, *dhatu*, and *srotopareeksha* assessment	✓			
Assessment of concomitant medications		✓	✓	✓
Assessment of rescue medications		✓	✓	✓
Assessment of adverse drug reactions and adverse events		✓	✓	✓
Drug compliance assessment		✓	✓	
Dispensing of trial drug and compliance reporting form	✓	✓		

### Trial Status and Dissemination Policy

Recruitment of study participants began in December 2023, shortly after procurement of the trial drug. The research findings will be disseminated through top-tier national and international peer-reviewed journals.

### Participant Withdrawal Guidelines

Participants will be withdrawn from the trial if they experience a serious adverse event, regardless of whether it is related to the trial drug or if they experience an adverse drug reaction that requires discontinuation of the trial medication. Acute illness requiring inpatient treatment during the study period, worsening of the existing condition, voluntary withdrawal from the study by parents, and drug compliance of less than 80% will also result in withdrawal from the study. The reason for withdrawal will be documented in the CRF, dated, and signed. Participants withdrawn from the trial will undergo a final examination if possible. If participants leave against medical advice, a final telephone interview will be conducted with the parents to assess the participant’s health status from the point of view of drug safety and the validity of study results.

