### Interventions

The drug *Aravindasava* has been procured from Indian Medicines Pharmaceutical Corporation Limited, a Good Manufacturing Practice–certified pharmaceutical company in Almora, Uttarakhand, with a quality assurance certificate ensuring compliance with the Ayurveda Pharmacopoeia of India standards [12]. The trial drug *Ayush-BR Leham* was prepared at the pharmacy of the Central Ayurveda Research Institute, Kolkata, as per the standard operating procedures developed by the Central Council for Research in Ayurvedic Sciences (CCRAS). The study drugs will be stored in a dark, cool, and dry place. The investigators will administer *Aravindasava* in both groups for 4 weeks at a dose of 5 mL twice daily after food, followed by *Ayush-BR Avaleha* in the study group at a dose of 5 g twice daily before food for 8 weeks. There will be no intervention in the control group after *Aravindasava* administration.

Both groups receive *Aravindasava*, ensuring that no group is disadvantaged in the early, critical phase, during which correction of digestion, absorption, and assimilation is necessary. All participants will receive standard nutritional care and public health interventions available to the general pediatric population with malnutrition during the study period. These include regular nutritional counseling by Accredited Social Health Activist workers or *Anganwadi* workers through government initiatives, age-appropriate dietary guidance from the study pediatrician, health check-ups and monitoring by the research team, management of infectious diseases that develop during the study, immunization, and routine health care. Both groups are advised to follow a home-prepared diet throughout the study. A home-prepared diet refers to age-appropriate, nutrient-dense meals that the family provides at home following personalized dietary counseling by the study team. It represents optimized nutrition within the family’s resources and cultural context. Compliance with the home-prepared diet will be recorded in the case report form (CRF).

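### The withdrawal rules end follow-up that the intention-to-treat primary analysis needs, and in weeks 5 to 12 the compliance rule can remove only study-arm children

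*Protocol article*

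**What the plan says.** Participant Withdrawal Guidelines lists the events that end participation. "Participants will be withdrawn from the trial if they experience a serious adverse event, regardless of whether it is related to the trial drug"; an adverse drug reaction that requires stopping the medication, acute illness needing inpatient care, "worsening of the existing condition" and parental choice have the same consequence. The list ends with adherence: "drug compliance of less than 80% will also result in withdrawal from the study". On what is collected afterwards, the section says: "Participants withdrawn from the trial will undergo a final examination if possible". Families who leave against advice get a telephone interview.

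Outcome Measures defines the primary outcome as the proportion of children whose WAZ changes by at least 0.5 "from baseline to weeks 12 and 16". Statistical Methods says that this outcome "will be analyzed using an intention-to-treat approach". For children who withdraw, are lost or "do not complete the week 12 assessment will be documented, and reasons for dropout will be recorded", with dropout reported by group.

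Interventions gives both arms Aravindasava for 4 weeks and then gives the study arm Ayush-BR Leham for 8 weeks. For the other arm it states: "There will be no intervention in the control group after" Aravindasava. Adherence to the home diet, which applies to both arms, is recorded but is not listed as a reason for withdrawal.

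**The concern.** An intention-to-treat comparison needs the week 12 and week 16 outcome of every randomised child, whatever the adherence or clinical course. The withdrawal section ends participation because of adherence or clinical course. A child withdrawn at week 6, say, has no outcome visit that the section commits to.

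Two features make this more than ordinary dropout.

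- **Unequal reach.** In weeks 5 to 12, two thirds of the 12-week treatment period, only study-arm children have a drug to be non-compliant with. Poor adherers can then be lost from that arm alone. If such families also feed their children less well or attend less often, those who remain in the study arm are a favourable selection.
- **Link to the outcome.** Worsening is close to the opposite of the primary outcome. The article gives no threshold for it, and it is judged in an open-label trial.

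At stake is whether the primary comparison estimates the effect of assignment, and in which direction it errs if it does not.

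**Working it through.** **The plan's own figure.** Sample Size gives 60% against 30% response, 80% power and 42 per group; Statistical Methods gives two-sided α = 0.05. With the pooled-variance formula:

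n = [1.96·√(2·0.45·0.55) + 0.8416·√(0.6·0.4 + 0.3·0.7)]² / 0.30² = (1.379 + 0.565)² / 0.09 ≈ 42. This reproduces.

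The stated 50 per group follows as 42 × 1.20 = 50.4. With 100 children at each of two centres and 1:1 allocation, there are about 100 per arm.

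**Inputs for the illustration.** From the article: 30% response (the control assumption, used here for both arms so that there is no true effect), 100 per arm and α = 0.05. Assumed, because the article does not give them: the fraction w of study-arm children withdrawn for compliance, their response rate r had they been followed, and 8% other loss at random in each arm.

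**Observed cases only.** The apparent study-arm rate is (0.30 − w·r)/(1 − w), against 0.30 in controls. The numbers analysed are n₁ = 100(1 − w)(0.92) and n₂ = 92. Type I error is from the normal approximation to the two-proportion test.

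| w | r | Apparent study-arm rate | Bias (points) | Type I error |
|---|---|---|---|---|
| 10% | 10% | 0.29/0.90 = 32.2% | +2.2 | about 6% |
| 13% | 10% | 0.287/0.87 = 33.0% | +3.0 | about 7% |
| 20% | 10% | 0.28/0.80 = 35.0% | +5.0 | about 11% |
| any | 30% | 30.0% | 0 | 5% |

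Worked line for w = 20%: n₁ = 73.6 and the pooled rate is 0.322. The null standard error is 0.0731 and the standard error at the apparent rates is 0.0733. The upper tail is Φ[(0.05 − 1.96·0.0731)/0.0733] = 0.102 and the lower tail is 0.004, together 10.6%. Simulation of the same scenarios agrees.

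The 13% row is the one to set beside the plan: 1 − 0.87 × 0.92 = 20% total study-arm loss, the attrition that Sample Size assumes. At w = 20% the total is 1 − 0.80 × 0.92 = 26%, which is above it.

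**Withdrawn children and other losses scored as failures.** The difference is 0.92(0.30 − w·r) − 0.92·0.30 = −0.92·w·r. For w = 20%:

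- r = 10%: −1.8 points, type I error about 6%.
- r = 30%: −5.5 points, type I error about 14%. Nearly all of this is rejection against the supplement; only about 0.2% is in its favour.

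The two analyses therefore err in opposite directions. For a given r they are not both at their worst: at r = 30% the observed-case analysis is unbiased, and at r = 10% failure scoring is only slightly off.

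**The case against.** Three stronger readings are tempting, and the document does not support them.

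- **That withdrawn children leave the analysis set.** The article does not say so. They may stay in the intention-to-treat set with missing or imputed outcomes, and the rules for that may sit in an analysis plan or full protocol that is not shown. Describing the remaining data as per-protocol in one arm presumes a complete-case analysis that is nowhere specified.
- **That no withdrawn child can have an endpoint.** Follow-Up Assessments schedules days 84 and 112 for all participants, and Table 1 still assesses compliance at week 12. The article does not say whether 80% is judged at each visit or over the whole course. A child judged non-compliant at day 84 could already have a week 12 WAZ, and earlier withdrawals leave fortnightly weights.
- **That every withdrawal rule removes children unequally.** The serious-adverse-event, inpatient and worsening rules are worded the same for both arms. If the supplement works, worsening might remove more poor responders from control, which would be conservative. The compliance rule itself applies to both arms in weeks 1 to 4.

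The size is also open to challenge. No compliance-withdrawal rate is documented. With 13% withdrawn and poor adherers responding at 20%, the observed-case bias is +1.5 points and type I error about 6%. With 13% withdrawn in the study arm and 6.5% in control (r = 10%), the bias is +1.6 points and type I error again about 6%. The article also calls the trial a pilot and exploratory.

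These points limit the claim but do not remove it. Withdrawal from the study is a rule that the article states, not a detail left out. The section names discontinuation of the medication separately, yet makes leaving the study the consequence. An analysis plan can specify imputation; it cannot recover weights that were not measured.

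**Conclusion.** The point holds in a limited form. As written, the withdrawal rules end participation for reasons of adherence and clinical course, while the primary analysis needs week 12 and week 16 WAZ for all randomised children. The sections must be reconciled. Only the compliance rule is structurally unequal, and only after week 4. The worsening rule matters for a different reason: it is tied to the outcome and applied without blinding.

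The document does not allow the bias to be quantified. If total study-arm loss matches the planned 20% and poor adherers respond at 10%, an observed-case analysis is off by about +3 points with type I error near 7%. Heavier compliance withdrawal (20%) gives +5 points and about 11%. With no link between adherence and response, the bias is zero. Failure scoring pushes the other way, by 1.8 to 5.5 points at 20% withdrawal. A reader should not take the larger error rates as expected values, nor add the two analyses' worst cases together.

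**What to change.** Leave the clinical criteria for stopping the drug as they are, and separate stopping the drug from leaving the study. State that a child who stops the drug, including for compliance below 80%, is still weighed at days 84 and 112 unless the parents withdraw consent. Apply this to children already withdrawn where those visits are still possible; Results says that enrolment is complete but the study is ongoing.

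Before analysis begins, state that all randomised children are analysed in their allocated arm. Where week 12 or week 16 WAZ is missing, impute it from the fortnightly weights already recorded, with a sensitivity analysis for departures from the imputation assumption. Use compliance of at least 80% only to define a per-protocol sensitivity set.

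Cost: an amendment, which under Protocol Amendments needs ethics approval (two committees approved the study); up to two already scheduled weighings per child; and, for children already withdrawn, renewed contact with the parents. The estimate will be somewhat diluted by non-adherence, as it is whenever the effect of assignment is the target. If the visits can no longer be held, the analysis statements can still be fixed in advance.
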